### Statistical analysis

All analyses will be performed using Stata 16. Prior to formal analysis, descriptive statistics and graphical displays will be used to identify missing and out-of-range values, assess distributional assumptions and identify outliers.

Recruitment bias will be assessed by comparing demographic and clinical characteristics of consenters and non-consenters using *t* tests (or Mann-Whitney) and chi-squared (or Fisher’s exact) tests as appropriate. Differential attrition will be assessed by comparing baseline characteristics of drop-outs and continuing participants using the same statistical tests.

### Outcome analysis

The primary analysis will follow the intention-to-treat principle and all study participants will be analysed as part of the study arm to which they were randomised in all outcome analysis. Missing data will be imputed using multiple imputation, redrawing 50 samples. Pearson’s chi squared test will be used to analyse study arm differences in the primary outcome. Linear regression will be used to analyse study arm differences for preparedness for decision-making at follow-up 1, illness communication at follow-up 1 and anxiety at follow-up. Each model will be adjusted for baseline and group assignment. Decisional conflict (follow-up 1), satisfaction (follow-ups 2 and 3) and regret (follow-ups 2 and 3) will be analysed using linear regression with group assignment as the independent covariate (equivalent to a test). The effect between groups and significance will be assessed using the beta-coefficient and *p* value corresponding to the group assignment term. Finally, prostate cancer-specific quality of life will be analysed with a random effects mixed model. The independent variables will be group assignment, time (coded 0/1) and the interaction term group assignment BY time. The effect and between groups and significance will be assessed using the beta-coefficient and *p* value corresponding to the interaction term. All results will be presented with 95% confidence intervals and a *p* value less than 0.05 (two-sided) will be deemed to be statistically significant.

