### Primary outcome

The primary outcome is self-reported uptake of AS as the first-line management option for LRPC assessed as a percentage (AS or curative treatment option) at follow-up 1.

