### Sample size

The sample size calculation was based on 80% power, a two-sided *α* = 0.05 test, and a difference in uptake of the AS treatment option of 15%. Assuming 65% uptake in the usual care group [3] and 80% uptake in the intervention group (a conservative assumption), the required sample size is 272 patients (136 in each study arm). Our sample size calculation was performed with PASS version 16. Allowing for 10% attrition, a total sample size of 304 participants is required.

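### The primary test, an unadjusted Pearson chi-squared on 50 imputed data sets, gives no effect estimate or confidence interval; a pooled, site-adjusted risk difference would give both

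*Protocol article*

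**What the plan says.** In the protocol article, Outcome analysis makes four statements that bear on the primary outcome:

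- Population: "The primary analysis will follow the intention-to-treat principle".
- Missing data: "Missing data will be imputed using multiple imputation, redrawing 50 samples".
- Test: "Pearson’s chi squared test will be used to analyse study arm differences in the primary outcome".
- Reporting: "All results will be presented with 95% confidence intervals", with significance declared when the p "value less than 0.05 (two-sided) will be deemed to be statistically significant".

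Under Primary outcome, uptake of active surveillance is binary and "assessed as a percentage (AS or curative treatment option) at follow-up 1". Under Sample size, the calculation rests on "80% power, a two-sided *α* = 0.05 test" and on a 15-point difference, 65% in usual care against 80% with the decision aid. Under Trial design and randomisation, allocation is one-to-one and stratified by recruitment site.

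For the linear and mixed models, Outcome analysis names the effect to be reported, a regression coefficient. For the primary outcome it names none.

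**The concern.** The stated test does not by itself produce the stated output. A Pearson chi-squared test yields a statistic and a p value. Rubin's rules need an estimate and its variance from each imputed data set, and the promised interval needs an effect measure to be an interval for. The article supplies an effect measure for every regression outcome but not for the primary one.

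Three things are at stake:

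- The trial could end with a primary p value and a separately derived interval that rest on different methods and can disagree near 0.05.
- If the 50 chi-squared results are combined informally, between-imputation variance is ignored and the test can reject too often.
- The design stratifies by site and the test does not use site. That is not invalid, but if uptake varies by site it tends to cost some precision.

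Timing matters too. The article says that statisticians will know the allocation before they prepare the flow diagram and the outcome analysis. An estimator still open at that point would be chosen with allocation known.

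**Working it through.** **Step 1: reproduce the plan's sample size.** Inputs from Sample size: 65%, 80%, 80% power, two-sided 0.05, 10% attrition. With unpooled variance:

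n per arm = (1.960 + 0.842)² × (0.65 × 0.35 + 0.80 × 0.20) / 0.15² = 7.849 × 0.3875 / 0.0225 = 135.2, so 136 per arm and 272 in all.

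Attrition: 136 / 0.9 = 151.1, so 152 per arm and 304 in all.

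Both figures match. The formula is built on a difference in proportions, which is the quantity that the primary analysis leaves unnamed.

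**Step 2: what each route delivers from 50 imputed tables.**

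- *Rubin's rules on the risk difference.* In imputation j, take the difference q_j and its variance u_j. The pooled estimate is the mean of the q_j. The total variance is T = Ū + (1 + 1/50)B, where Ū is the mean of the u_j and B is the variance of the q_j. With r = (1 + 1/50)B/Ū, the reference is t with 49(1 + 1/r)² degrees of freedom. This gives an estimate, an interval and a p value.
- *D2 rule on the chi-squared statistics X_j.* With r = (1 + 1/50) × var(√X_j), D2 = [mean(X_j) − (51/49) r] / (1 + r), referred to F with 1 and 49(1 + 1/r)² degrees of freedom. This gives a p value only.
- *Informal rules.* Compare the mean of the X_j with 3.84, take the median p value, or use one imputed set. These give a p value only.

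**Step 3: simulation.** 152 per arm, 65% in both arms, 50 proper imputations drawn within arm, outcome missing completely at random, 40,000 trials (Monte Carlo standard error about 0.1 point). Only the 10% column uses a missing fraction from the article; 5% and 20% are assumptions.

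| Type I error | 5% missing | 10% missing | 20% missing |
|---|---|---|---|
| Rubin's rules, risk difference | 5.3% | 5.1% | 5.3% |
| D2 rule | 5.2% | 4.9% | 5.1% |
| Mean p value | 5.2% | 5.0% | 5.2% |
| Median p value | 5.8% | 6.3% | 8.1% |
| Mean chi-squared against 3.84 | 6.0% | 6.7% | 9.1% |
| One imputed set | 6.4% | 7.6% | 11.0% |

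Two further runs of 20,000 trials, one at 65% and one at 72.5% in both arms, gave 6.7% to 6.8% for the mean statistic and 6.4% to 6.5% for the median at 10% missing. The range for these two rules across all runs is therefore 6.3% to 6.8%.

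**Step 4: power at 65% against 80%, 10% missing.** Rubin's rules 80.1%, D2 79.7%, complete-case chi-squared 79.8%. Under these rates the mean-statistic rule and the Rubin-pooled difference reach different verdicts in 3.1% of trials at 10% missing, and in 7.3% at 20% (assumed).

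All these models are unadjusted. The effect of adding site was not simulated, because the article gives no uptake rates by site.

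**The case against.** The strongest reply has four parts.

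*The article never says that the chi-squared results will be averaged or otherwise combined informally.* This stands. A reader might infer that the plan as written inflates type I error, but the text does not support that. It fixes no combining rule, and a condensed article may leave that rule to the full protocol or the analysis plan. Its absence alone is not a defect.

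*Valid routes exist under the stated test.* This also stands. D2 holds its size at every missing fraction examined. For a two-by-two table, Pearson's statistic is the squared difference in proportions divided by its pooled variance, so the ingredients for Rubin's rules are in each imputed table. Pooling that difference with that variance gave 4.8% to 5.1% type I error at 5% to 30% missing (72.5% in both arms, 20,000 trials). A reader might infer that the chi-squared and multiple imputation cannot be reconciled; they can.

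*A difference in percentages with an interval, set beside a chi-squared p value, is ordinary reporting, and the promise of intervals covers it.* This stands in part. Nothing in the text forbids it. But the article does not name the difference as the effect measure, and the p value and interval would then come from different calculations.

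*At the one missing fraction that the article gives, even the informal mean and median rules add little.* Agreed: about 1.3 to 1.8 points above 5%. The larger figures need missing fractions that the article does not state.

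What remains is the mismatch between the named test, the imputation and the promised interval, and the unused site stratification.

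**Conclusion.** The point holds as a should-fix improvement, not a must-fix error. The article's primary analysis names a test that gives neither an estimate nor an interval, while promising intervals for all results and sizing the trial on a risk difference. Valid pooling of the chi-squared statistics gives about 4.9% type I error at 10% missing, but no estimate or interval. Inflation to about 6.3% to 6.8% is a conditional risk under mean or median combining, not a property of the plan.

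The pooled risk difference has 5.1% type I error and 80.1% power at 10% missing, and its p value and interval agree by construction. These figures assume outcomes missing completely at random, imputation within arm and no site adjustment. The totals of 272 and 304 stand.

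**What to change.** Make the primary analysis a risk difference between arms from a binomial or logistic model with arm and site (standardised to the risk-difference scale if logistic). Estimate it in each of the 50 imputed data sets and pool the estimate and standard error by Rubin's rules. Take both the primary p value and the 95% confidence interval from that pooled estimate. Name the risk difference as the primary effect measure, and settle this before statisticians see the allocation.

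The cost is a changed sentence in the plan and a few lines of Stata. The one practical difficulty is very small sites, where site terms may not be estimable; these may need to be grouped by a rule set in advance. No extra data or participants are needed.

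Optional: state that imputation is done within arm, and keep the chi-squared test as a complete-case sensitivity analysis.

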**Methods:**

Three hundred four men and their partners are randomly assigned one-to-one to *Navigate* or to the control arm. Randomisation is electronically generated and stratified by site. *Navigate* is an online decision aid that presents up-to-date, unbiased information on LRPC tailored to Australian men and their partners including each management option and potential side-effects, and an interactive values clarification exercise. Participants in the control arm will be directed to the website of Australia’s peak national body for prostate cancer. Eligible patients will be men within 3 months of being diagnosed with LRPC, aged 18 years or older, and who are yet to make a treatment decision, who are deemed eligible for AS by their treating clinician and who have Internet access and sufficient English to participate. The primary outcome is self-reported uptake of AS as the first-line management option. Secondary outcomes include self-reported preparedness for decision-making; decisional conflict, regret and satisfaction; quality of illness communication; and prostate cancer-specific quality of life. Uptake of AS 1 month after consent will be determined through patient self-report. Men and their partners will complete study outcome measures before randomisation and 1, 3 and 6 months after study consent.

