### Trial design and randomisation

This study will use a parallel group, prospective randomised controlled trial (RCT) with one baseline and three post-baseline assessments (i.e. follow-ups 1, 2 and 3), along with economic and web analytics substudies. In this study, ‘partner’ refers to the support person nominated by the patient. Both patients and their partners (if one is nominated) will be invited to participate. Following informed consent and completion of baseline study measures, participating patients and their partners will be randomly assigned to *Navigate* or the usual care arm with a one-to-one allocation, stratified by recruitment site. Randomisation will be undertaken remotely and independently by the trial coordinator using a purpose-built Microsoft Access randomisation database. After a participant (patient/partner) has been enrolled and completed baseline measures, the trial coordinator uses the randomisation database to assign the participant to the intervention or usual care arm and informs them via email of the experimental allocation. Post-baseline assessments will occur approximately 1, 3 and 6 months after consent. Participants will be informed of their allocation after completing baseline questionnaires. Researchers involved in data collection will be blinded to group allocation. Statisticians will be unblinded to allocation before preparation of the participant flow diagram and outcome analysis. Ethical approval was received from the Peter MacCallum Cancer Centre Human Research Ethics Committee (HREC16 PMCC114). Figure 1 displays the enrolment, group allocation, intervention and assessment schedule.

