#### Eligibility criteria

Men will be eligible to participate in this trial if they are 18 years or older; have been diagnosed with LRPC in the last 3 months and have yet to make a treatment decision; have been deemed eligible for AS by their treating clinician; and have Internet access and sufficient English to complete study requirements and use the *Navigate* website. Men will be ineligible if they have a severe psychiatric or cognitive disorder or are too unwell to participate as deemed by their treating clinician, self-report, or the research team at the time of approach.

Partners are eligible to participate in this trial if they are 18 years or older, are the designated partner identified by the consenting patient and have Internet access and sufficient English to complete study requirements and use the *Navigate* website.

Participating sites include five Australian treatment centres within Victoria (Peter MacCallum Cancer Centre, Western Hospital, Cabrini Hospital, Alfred Hospital, Austin Hospital) and two in Queensland (Royal Brisbane and Women’s Hospital, Redcliffe Hospital). Men with LRPC and their partners from either public or private health care settings are also able to self-refer online to the trial.

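### Site stratifies the randomisation but is in no listed analysis: the unadjusted primary test stays valid, yet may be conservative and gives up some precision

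*Protocol article*

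**What the plan says.** Under Trial design and randomisation, patients and partners are allocated "with a one-to-one allocation, stratified by recruitment site". The Methods part of the abstract agrees: "Randomisation is electronically generated and stratified by site". Under Eligibility criteria there are seven hospitals (five in Victoria, two in Queensland), and men from public or private care "are also able to self-refer online to the trial". The article does not say which stratum a self-referred man belongs to.

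Under Outcome analysis, the primary analysis is fixed: "Pearson’s chi squared test will be used to analyse study arm differences in the primary outcome". The terms of the other models are listed as follows.

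- Preparedness, illness communication and anxiety: "Each model will be adjusted for baseline and group assignment".
- Decisional conflict, satisfaction and regret: these "will be analysed using linear regression with group assignment as the independent covariate".
- Prostate cancer-specific quality of life: a random effects mixed model with group, time and their interaction. Its random effects are not named.

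The exploratory outcomes use regression of the same kind. Site is not named in any analysis.

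**The concern.** Stratifying by site makes the arms alike in site mix. If site predicts the outcome, the true variance of the arm difference is then smaller than under simple randomisation. A test that ignores site does not use this: it counts between-site variation as error. The result is a standard error that is too large, an actual type I error below 5%, and less power than a stratified test would have on the same data.

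The article goes further than leaving covariates to a later plan. It names the primary test and lists the model terms, so an analysis plan that follows it would leave site out, and one that adds site would depart from it. At stake is the precision that stratification was meant to buy.

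**Working it through.** **1. The plan's own figure.** Inputs from the Sample size section: 65% and 80% uptake, two-sided alpha 0.05, 80% power. With the unpooled two-proportion formula,

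n per arm = (1.960 + 0.842)² × (0.65 × 0.35 + 0.80 × 0.20) / 0.15² = 7.849 × 0.3875 / 0.0225 = 135.2, so 136 per arm and 272 in total, as stated.

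For 10% attrition, 136 / 0.9 = 151.1, so 152 per arm and 304 in total, as stated. The sample size is that of an unstratified comparison, consistent with the Pearson test.

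**2. Why the unadjusted standard error is too large.** Let p_k be the uptake at site k and p the overall uptake. Then

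p(1 − p) = mean of p_k(1 − p_k) + Var(p_k).

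Pearson's test uses the left side. With exact balance within site, the sampling error of the arm difference contains only the first term on the right. Under no effect, the ratio of true to assumed standard error is r = √[1 − Var(p_k) / (p(1 − p))], and the actual type I error is about 2 × [1 − Φ(1.96 / r)].

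At p = 0.65, p(1 − p) = 0.2275. The SD of site uptake is a range I assume, because the article gives none. Normal site log-odds with SD 0.5, 1.0 and 1.5 correspond to site uptake SDs of about 10.8, 19.4 and 25.4 points.

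| SD of site log-odds | Var(p_k) | r | Type I error (formula) |
|---|---|---|---|
| 0.5 | 0.0118 | 0.974 | 4.4% |
| 1.0 | 0.0375 | 0.914 | 3.2% |
| 1.5 | 0.0643 | 0.847 | 2.1% |

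**3. Simulation.** 272 men, eight equal strata of 34 (seven hospitals plus self-referral, an assumption), exact 1:1 within stratum, site log-odds normal, marginal uptake held at 65% and 80%, 40,000 runs per setting. Pearson is compared with Cochran-Mantel-Haenszel (CMH) by site.

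| SD of site log-odds | Power, Pearson | Power, CMH | Type I error, Pearson |
|---|---|---|---|
| 0 | 80.3% | 80.1% | 5.1% |
| 0.25 | 80.0% | 80.0% | 4.9% |
| 0.5 | 80.7% | 81.6% | 4.6% |
| 0.75 | 80.8% | 82.8% | 3.9% |
| 1.0 | 81.6% | 85.0% | 3.5% |
| 1.5 | 82.3% | 88.8% | 2.4% |

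CMH type I error stays between 4.8% and 5.1%. Unequal strata (10 to 80 men) give nearly the same results: at SD 1.0, power is 81.4% against 84.7% and Pearson type I error 3.5%. A separate simulation of the same design put Pearson type I error at 4.3% for SD 0.5 and 2.9% for SD 1.0, with a gain of about 4 points of power at SD 1.0. The ranges quoted in this point span these runs.

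**4. Dependence on balance.** With simple allocation inside each stratum in place of exact balance, Pearson type I error is 4.9% when site uptake has an SD of 15 points and 4.8% at 22 points. The conservatism then all but vanishes, though a stratified test still gains some power.

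**The case against.** The strongest reply is that nothing invalid has been planned. Pearson's test matches the sample size calculation, any error is on the safe side, and power stays at 80.0% to 82.3% in every equal-strata setting above. This stands, and it limits the point to efficiency.

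Next, the size of the loss is unknown. The article says only that uptake of active surveillance varies widely around the world, not between these hospitals or between public and private care. All men entered are judged eligible for surveillance and are still undecided, which could narrow site differences. The article also gives no blocking or minimisation method, so tight balance within site is assumed. Both replies stand.

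Third, a site random effect in the quality-of-life model cannot be excluded, and a full protocol (V8) exists that is not shown here. That holds for the quality-of-life model. It does not remove the mismatch for the named primary test or for the regressions whose terms are listed.

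A reader might also infer that omitting site leaves the trial underpowered. A simulation that fixes the within-site odds ratio at 2.15 (0.80/0.20 divided by 0.65/0.35) while sites spread apart does show Pearson power of 72.0% at a site SD of 15 points and 63.2% at 22 points. That is not the cost of omitting site. Holding the odds ratio fixed shrinks the marginal difference below 15 points, to about 13.3 and 12.5 in a re-run, and the stratified test falls too, to 74.9% and 70.8%. Only the gaps, 74.9 − 72.0 = 2.9 and 70.8 − 63.2 = 7.6 points, belong to the choice of test.

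**Conclusion.** The mismatch is in the text: site stratifies the allocation, and no listed analysis term is site. The consequence is modest, and its direction is conservative. If sites differ and the arms are balanced within site, the unadjusted test rejects too rarely under no effect (about 4.3% to 4.6% at a site log-odds SD of 0.5, and 2.9% to 3.5% at SD 1.0). Relative to a stratified test it gives up about 0 to 1 points of power up to SD 0.5, about 2 to 4 at SD 0.75 to 1.0, and about 6 to 8 at SD 1.5.

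These figures rest on three assumptions that the article does not settle: the between-site variation, the eight strata, and exact balance within each. The documents do not support a claim of inflated false positives, of a shortfall against the planned 80% power, or that uptake is known to depend on site. The change is worth making because it costs almost nothing if sites do not differ.

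**What to change.** Before unblinding:

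- Make the primary analysis a logistic or binomial regression of uptake on arm plus the randomisation stratum as actually used, stating where self-referred men fall. Report the marginal risk difference with its 95% interval, pooled over the 50 imputations. A CMH test stratified by site is an alternative.
- Add the stratum to the secondary and exploratory models, and name the random effects of the quality-of-life model.
- Set in advance a rule for pooling very small sites.

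The regression also provides the confidence interval that the Outcome analysis section promises for all results. Its coefficient pools directly over imputations, which a chi-squared statistic does not.

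The cost is more than editing: recruitment opened in May 2017, so replacing the named primary test must be documented and dated as a change made before unblinding. No new data are needed, since site is already recorded for randomisation, and the sample size of 272 does not change. If sites do not differ, the loss of power is negligible (80.3% against 80.1%).

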### Treatment decision making in LRPC

Management decision making is difficult for men with LRPC. Decision-related distress and confusion are high [23–25], due largely to the variety of management options with no clear best choice and the fact that management decisions are highly dependent on men’s individual preferences and lifestyle [26]. For those contemplating AS, anxiety about not receiving radical (i.e. curative) treatment is common [24]. Most men do not consider all management options nor do they make decisions concordant with their personal preferences and values [27, 28]. Partners of men with LRPC also experience high decisional distress and confusion [15, 29], and some pressure their partner towards curative treatment [24, 28]. The study anticipates that both men and their partners would benefit from decision-making support, particularly regarding their understanding of the benefits and risks associated with each management option, the risk of the LRPC spreading outside the prostate and the concordance of each option with their personal values and preferences [27].

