### Main study measures

#### Demographic and clinical information

Demographic information collected from patients and partners includes age (in years), marital status, postcode, highest education level, occupation and ethnic origin.

Clinical information (Gleason score and PSA) is obtained from the referring site or the referring clinician or collected via a medical record audit.

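### The primary comparison is an unadjusted chi-squared test although likely predictors of the choice are collected: a small, free gain in precision is forgone, with no shortfall in power

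*Protocol article*

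**What the plan says.** The primary outcome is self-reported first-line management (AS or curative treatment) at follow-up 1. Under Outcome analysis, Pearson's "chi squared test will be used to analyse study arm differences in the primary outcome". Missing values are to be filled by multiple imputation with 50 draws; the variables in the imputation model are not given. The same section adjusts illness communication and anxiety for their baseline values and promises 95% confidence intervals for all results.

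The Background (Treatment decision making in LRPC) describes what moves the choice. Among men contemplating AS, "anxiety about not receiving radical (i.e. curative) treatment is common", and some partners press towards curative treatment.

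Several related variables are recorded. Age is in the demographic data. "Clinical information (Gleason score and PSA) is obtained from the referring site or the referring clinician", or through a record audit. PROMIS anxiety is measured at baseline (Secondary outcomes). Men may take part with or without a partner, and enrolled partners are randomised with the man after baseline measures, so partner participation is known by then (Participants and study setting; Trial design and randomisation). The article gives baseline characteristics one role, the comparison of drop-outs with continuing participants, and uses demographic and clinical characteristics to compare consenters with non-consenters (Statistical analysis). None enters the primary comparison.

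On size: "Assuming 65% uptake in the usual care group [3] and 80% uptake in the intervention group", with 80% power and a two-sided 5% test, 136 men per arm are needed. "Allowing for 10% attrition, a total sample size of 304 participants is required".

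**The concern.** A baseline variable that predicts the outcome can sharpen the treatment comparison at no cost in patients. Here the article names two influences on the choice, measures one of them directly (anxiety) and has a rough proxy for the other (partner participation, which is not the same as partner pressure). It then selects a primary test that can use neither. Some secondary outcomes receive baseline adjustment while the primary outcome does not.

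Two practical points add to this. A Pearson test gives no confidence interval, although one is promised for every result, and its statistic does not combine across imputed data sets by the usual rules for estimates and standard errors. A model-based risk difference answers both, on the scale on which the trial was sized. An unadjusted risk difference would answer them too, so this supports estimating a difference more than it supports adjusting.

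At stake is some precision in a trial planned at exactly 80% power. The validity of the comparison is not in question. Site, the stratification factor, is a separate matter and is left aside here.

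**Working it through.** **1. Inputs from the Sample size section.** Uptake 0.65 and 0.80, difference 0.15, two-sided alpha 0.05 (z = 1.960), power 80% (z = 0.842), 136 per arm, 10% attrition.

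**2. Reproducing the plan's figures.** With unpooled variance, n per arm = (1.960 + 0.842)² × (0.65 × 0.35 + 0.80 × 0.20) / 0.15² = 7.849 × 0.3875 / 0.0225 = 135.2, so 136 per arm and 272 in total. With pooled variance under the null, n is 138 per arm (276). Attrition: 136 / 0.9 = 151.1, so 152 per arm and 304 in total. Both stated totals reproduce for an unadjusted two-proportion comparison.

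**3. Power of the unadjusted test at 136 per arm.**
- SE = √(0.3875 / 136) = 0.0534. Unpooled power = Φ(0.15 / 0.0534 − 1.960) = 80.2%.
- Null SE = √(2 × 0.725 × 0.275 / 136) = 0.0541. Pooled power = Φ((0.15 − 1.960 × 0.0541) / 0.0534) = 79.4%.

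The planned 80% is met to within rounding of the formula. With 152 per arm observed, the pooled figure is 83.7%.

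**4. What adjustment could add: approximation.** The article does not say how strongly any covariate predicts the choice, so the share of within-arm outcome variance explained (R²) is an assumption. Multiplying both standard errors by √(1 − R²) in the pooled formula at 136 per arm gives:

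| Assumed R² | Power | Gain over 79.4% |
|---|---|---|
| 0.02 | 80.3% | 0.9 |
| 0.05 | 81.5% | 2.1 |
| 0.10 | 83.5% | 4.1 |

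**5. What adjustment could add: simulation.** 5000 trials per setting, 136 per arm, marginal uptake 65% and 80%. The Pearson test is compared with a logistic model on arm plus one normally distributed baseline score.

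| Odds ratio per SD of score | R² (control / Navigate) | Pearson | Adjusted logistic | Difference |
|---|---|---|---|---|
| 1.00 | 0 / 0 | 79.1% | 78.3% | −0.8 |
| 1.42 | 0.027 / 0.019 | 80.0% | 80.5% | +0.5 |
| 1.65 | 0.052 / 0.038 | 79.2% | 79.8% | +0.6 |
| 2.12 | 0.105 / 0.082 | 79.9% | 82.4% | +2.5 |

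The Monte Carlo standard error of each power is √(0.8 × 0.2 / 5000) = 0.6 points, so differences below 1 point should not be over-read. A separate run of 3000 trials per setting gave adjusted power of 80.0% at R² = 0.034 and 82.8% at R² = 0.093, against 79% to 81% unadjusted. The simulations fit the model that would actually be used and show smaller gains than the approximation, so the size rests on them: about 0 to 3 points for R² of roughly 0.02 to 0.09. The single score stands for the whole covariate set; several separate covariates cost a few more degrees of freedom, which is a reason to keep the list short.

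**The case against.** The best defence is that nothing here is wrong. Under randomisation an unadjusted comparison of two proportions is valid, and it matches the basis on which the trial was sized. The 10% allowance leaves 304 × 0.9, about 273 men, so the planned 272 are available even if imputation recovers nothing. All men have low-risk disease and are judged suitable for AS, so PSA and Gleason score may vary little and predict little. The article gives no timing for these two values and allows them to come from a record audit, so they cannot be assumed to be pre-randomisation values for every man. All of this stands, and it limits the point to an improvement.

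Three stronger readings are tempting, and the document does not support them.

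- *A reader might infer that the trial loses power.* It does not: the sample size was calculated for the unadjusted comparison and delivers its stated power.
- *A reader might infer that the imputation is weak.* The imputation variables are not stated. An article may leave them to the full protocol or analysis plan, and they may include these covariates. They may also include later data that bear on the choice made, such as EPIC-26 at every follow-up or Medicare service records for consenting men.
- *A reader might infer that a baseline question on which option the man favours should be added.* None is listed, but this is a condensed article. Trial status gives recruitment from May 2017 to an expected close in December 2020, with the current protocol dated 27 March 2020. Even an item added then would cover about 9 of 44 months, or some 20% of men under even accrual. Any gain that assumes near-complete collection is out of reach.

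**Conclusion.** The point holds as a free improvement. The primary test ignores baseline information that the trial already gathers and that the article itself links to the choice. The size is small: about 0 to 3 points of power if the collected covariates explain roughly 2% to 9% of the outcome, and under 1 point lost if they explain nothing. That range is assumed, since the document gives no prognostic strength for any of these variables. There is no deficit against the planned 80%, no bias and no error in the stated sample size.

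**What to change.** Before the statisticians are unblinded, which the article places ahead of the participant flow diagram and the outcome analysis, write into the analysis plan:

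- Primary analysis: a logistic model for AS uptake at follow-up 1 with group and a short fixed list of baseline covariates: PROMIS anxiety, partner participation as recorded at randomisation, age, and PSA and Gleason score where these are pre-randomisation values.
- Effect measure: the standardised risk difference with 95% confidence interval, pooled over the 50 imputations. This keeps the result on the scale of the 15-point difference used for sizing.
- Imputation: include the same covariates in the imputation model.
- Supporting analysis: the Pearson test as now planned.

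The cost is wording and a little programming, with no new data, patients or visits. Timing is the one constraint: covariates chosen after unblinding would invite the charge that they were picked for the result.
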